**Methods/Design:**

HPV.edu is a cluster randomised trial of a complex intervention in schools aiming to recruit 40 schools with year-8 enrolments above 100 students (approximately 4400 students). The schools will be stratified by Government, Catholic, and Independent sectors and geographical location, with up to 20 schools recruited in each of two states, Western Australia (WA) and South Australia (SA), and randomly allocated to intervention or control (usual practice). Intervention schools will receive the complex intervention which includes an *adolescent intervention* (education and distraction); *a decisional support tool* for parents and adolescents and *logistical strategies* (consent form returns strategies, in-school mop-up vaccination and vaccination-day guidelines). Careful process evaluation including an embedded qualitative evaluation will be undertaken to explore in depth possible mechanisms for any observed effect of the intervention on primary and secondary outcomes.

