### Statistical methods/analysis

#### Power calculation

To allow for the possibility of schools dropping out of the study, we increased the number of schools by 10 % and aimed to recruit a total of 40 schools. A total of 36 schools allows for the detection of a change in the percentage of students vaccinated from 70 to 80 % at a significance level of 0.05 and with a power of 80 % and assuming an intraclass correlation coefficient (ICC) of 0.05 [36]. We estimated the ICC from a pilot study in NSW to be 0.04, and other cluster trials of adolescent health behaviours have reported ICC’s of less than 0.05 [37]. We estimated, that on average, each school of the 36 schools would have 150 students giving a total final sample size of 5400 students.

With a total of 36 schools, we will be able to detect the following differences in means between the intervention and control groups for the four secondary outcomes: 1) Knowledge–minimum detectable difference “equals” = 0.7; 2) Fear/anxiety–minimum detectable difference “equals” = 0.7; 3) Decision making–minimum detectable difference “equals” = 0.5; 4) Skills inventory–minimum detectable difference “equals” = 18; all assuming an ICC of 0.05, power of 80 %, significance of 0.05 and standard deviations derived from a pilot study evaluating each of these measures and allowing for a 40 % non-completion of these outcomes [36, 37].

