#### Primary outcome analysis

The primary analysis will compare vaccination rates using the Mantel-Haenszel method, taking into account the stratification by year, state and school sector and adjusted for clustering [36]. In addition, logistic regression models will be used to adjust for baseline vaccination rates (average of the previous 2 years), school type (single-sex, or mixed), school size and SEIFA index using generalized estimating equations (GEE) with robust standard errors. The level of implementation of the intervention will also be included.

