#### Secondary outcome analysis

Mean change in scores of knowledge, self-efficacy, fear/anxiety, and decision-making will be compared between groups using two-sample t-tests with appropriate adjustment for clustering. Baseline scores for knowledge will be taken from the control group. Proportion of consent form returns will be compared between groups prior to dose 1 using Chi-square test with appropriate adjustment for clustering. Time taken to vaccinate will be measured by nurses during each immunisation day in both intervention and control schools. It will be calculated as the mean time to vaccinate 50 students in intervention schools compared with control schools. Mean time to vaccinate will be compared between groups in both years of the study to determine effect of the intervention over time. We will investigate whether the intervention improves vaccination rates through its effect on fear reduction, and self-efficacy increase, by comparing estimates of the effect of the intervention both with and without adjustment for the possible intermediary variables of fear/anxiety, and self-efficacy. These logistic regression models will use GEE and robust standard errors to account for the clustering.

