#### Process evaluation

Implementation of intervention*Teachers and nurses logs*: During the intervention, school personnel and immunisation nurses will complete study logs. The first log will document the implementation of the education intervention to be completed by school personnel, the second log will document vaccination day processes to be completed by immunization nurses, and the third log will document logistics implemented and observed by supervising school personnel on vaccination day.Qualitative evaluationWe will undertake this in a sub-sample of intervention and control schools, which we term the ‘case-study schools’. Data collection will include observations of vaccination day, semi-structured interviews with teachers, school nurses, immunisation nurses and parents, and semi-structured focus groups with students to provide a more in-depth understanding of the mechanisms for change promoted by the intervention. The interviews and focus groups will be conducted primarily to explore the effects of the study intervention and what aspects of the intervention are most useful and what aspects are less useful. Qualitative ethnographic methods have been used with success to evaluate previous similar investigations [6, 14].Six intervention schools and 6 control schools will serve as case studies during the study. Case studies are detailed analyses of persons, events, decisions, projects, policies, institutions, programs, interventions or other systems that are studied holistically [38]. Case studies can draw on qualitative and quantitative data to provide in-depth examples of schools as sites in which knowledge, perceptions and experiences of HPV and HPV vaccination are effectively contextualised. This method will allow better explanation of the effects of the intervention by comparing and contrasting case studies.We aim to recruit 6–10 students for at least one focus group and 6–8 parents for one focus group or at least 4 individual interviews in each case study school. We will interview at least one school personnel member and at least one immunisation nurse for each selected school. If data collected from one school is insufficient for data saturation, then an additional school may be recruited.All qualitative data will be digitally recorded, and transcribed verbatim. The qualitative evaluation aims to explore in depth possible mechanisms for any observed effect of the intervention on primary and secondary outcomes. We will analyse the qualitative data using thematic and discourse analysis [39–42].

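### The adjusted regression of vaccination uptake is to include the level of implementation, a consequence of allocation, so its arm coefficient would not estimate the effect of allocation

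*Protocol article*

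**What the plan says.** Under Primary outcome analysis, the protocol article states: "The primary analysis will compare vaccination rates using the Mantel-Haenszel method". That comparison accounts for the stratification by year, state and sector and for clustering. No implementation term is mentioned in it.

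The section goes on: "In addition, logistic regression models will be used to adjust for baseline vaccination rates (average of the previous 2 years". The remaining covariates are single-sex or mixed school, school size and the SEIFA index, fitted by GEE with robust standard errors. The next and last sentence is "The level of implementation of the intervention will also be included".

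Process evaluation shows where implementation is recorded: "During the intervention, school personnel and immunisation nurses will complete study logs". Of the three logs, "The first log will document the implementation of the education intervention to be completed by school personnel". The second covers vaccination-day processes and the third vaccination-day logistics. Schools are "randomly allocated to intervention or control (usual practice".

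Secondary outcome analysis treats two other post-randomisation variables differently. It plans on "comparing estimates of the effect of the intervention both with and without adjustment for the possible intermediary variables of fear/anxiety, and self-efficacy".

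**The concern.** The four listed covariates describe a school before it is randomised. Adjusting for them keeps the randomised comparison and can sharpen it. Level of implementation is of another kind: it is observed after randomisation, is largely determined by arm, and is the means by which the programme is meant to raise uptake. With arm and implementation in one model, the arm coefficient contrasts the arms at the same implementation level. That is not the effect of being allocated to the intervention.

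Three things can follow. The part of the effect that runs through implementation is taken out of the arm coefficient. If well-organised schools both implement better and vaccinate more, conditioning on implementation brings in confounding that randomisation had removed. And because implementation is correlated with arm, the arm coefficient is less precise.

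These are the only covariate-adjusted models that the article specifies for the primary outcome. Followed literally, an effective programme could produce an adjusted odds ratio near 1, with a wide interval, beside a positive Mantel-Haenszel result.

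**Working it through.** **The plan's own figure.** Power calculation gives 36 schools for "detection of a change in the percentage of students vaccinated from 70 to 80" per cent, with alpha 0.05, power 80%, ICC 0.05 and 150 students per school. Taking alpha as two-sided, schools per arm are

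c = 1 + (1.96 + 0.84)² × [0.21/150 + 0.16/150 + 0.05 × (0.21 + 0.16)] / 0.10² = 17.5, so 18 per arm and 36 in all.

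The figure is reproduced, and this point does not alter it.

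**Loss of precision.** The article gives no implementation score, so every score below is an assumption on a 0 to 1 scale. With equal arms, let B = (difference in mean score)²/4 and W = the average within-arm variance. Then r² = B/(B + W), the variance inflation is 1/(1 − r²), and the standard error grows by its square root. This is the linear-model approximation.

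| Control mean (SD) | Intervention mean (SD) | B | W | r | Variance inflation | SE multiplier |
|---|---|---|---|---|---|---|
| 0.3 (0.2) | 0.7 (0.2) | 0.040 | 0.040 | 0.707 | 2.0 | 1.41 |
| 0 | uniform 0 to 1: 0.5 (0.289) | 0.0625 | 0.0417 | 0.775 | 2.5 | 1.58 |
| 0 | 0.6 (0.3) | 0.090 | 0.045 | 0.816 | 3.0 | 1.73 |
| 0.1 (0.1) | 0.7 (0.25) | 0.090 | 0.036 | 0.844 | 3.5 | 1.87 |
| 0 | 0.7 (0.25) | 0.1225 | 0.031 | 0.893 | 4.9 | 2.22 |
| 0 | 0.8 (0.2) | 0.160 | 0.020 | 0.943 | 9.0 | 3.00 |
| 0 | uniform 0.5 to 1: 0.75 (0.144) | 0.1406 | 0.0104 | 0.965 | 14.5 | 3.81 |

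A contrast with 80% power has an expected z of 2.80. If the arm term kept the whole effect, power would be Φ(2.80/1.41 − 1.96) = 51% in the first row, Φ(2.80/1.58 − 1.96) = 43% in the second, and 11% in the last. The 80% starting point is itself an assumption here, because the article does not attach its power to the GEE model.

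**Bias.** A simulation used 36 schools of 150 students, a school-level variance set to match the ICC of 0.05, and a conditional log odds ratio of ln(0.8/0.2) − ln(0.7/0.3) = 0.54. The model was logistic with cluster-robust standard errors, with 400 replicates per scenario. Four score distributions were used, written as control mean (SD) against intervention mean (SD) and truncated to 0 to 1: 0 against 0.7 (0.25); 0 against 0.8 (0.15); 0.1 (0.1) against 0.7 (0.25); 0.3 (0.2) against 0.7 (0.2). Before truncation the second has a variance inflation of 1 + 0.16/0.01125 = 15.2, close to the top of the table. Ranges run over the four distributions; significance counts either direction.

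| Assumption | Arm log OR without the term | Significant | Arm log OR with the term | Significant |
|---|---|---|---|---|
| Whole effect through implementation | 0.49 to 0.51 | 77% to 84% | −0.03 to 0.02 | 9% to 13% |
| Half through it | 0.50 to 0.52 | 79% to 83% | 0.25 to 0.30 | 14% to 27% |
| None through it | 0.50 to 0.52 | 83% to 86% | 0.50 to 0.56 | 21% to 55% |
| Any of these shares, with better-uptake schools implementing better (correlation 0.4) | 0.48 to 0.52 | 65% to 85% | −1.00 to 0.10 | 11% to 51% |

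In the last row many of the significant results point the wrong way. Only when none of the effect runs through implementation, and implementation is unrelated to school quality, is the arm coefficient unbiased; even then it loses much of its precision.

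**The case against.** **The primary analysis.** A reader might infer that the randomised comparison is lost. The article does not support that. The Mantel-Haenszel comparison is named as primary, comes first and carries no implementation term; the regression is additional. This objection stands in full and limits the severity.

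**Near-identity with arm.** A reader might also infer that implementation is almost the same variable as arm, with control schools at zero. That is plausible for the film, magazine and decision tool, which control schools do not receive. But the score is undefined, two of the three logs concern vaccination day, and all schools follow state procedures for consent forms, room set-up and mop-ups. If the score counts those, control schools need not be near zero and the correlation may be nearer 0.7. This stands too, but the fault does not need near-identity: a post-randomisation variable on the pathway is enough.

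**Another meaning of the sentence.** It could describe a further model, or a graded exposure of control, low and high implementation. The wording does not exclude this, and an analysis plan might settle it. As printed, though, it follows the covariate list directly, says that implementation is also included, and gives no separate, exploratory or intervention-only label. A graded exposure would not restore the randomised contrast either, since schools are not randomised to low or high.

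**Coding.** If the score were centred at its mean within intervention schools and set to zero in controls, the arm coefficient would be the effect at average implementation, with little collinearity. That is correct, but the article fixes no such coding, and centring over all schools would leave the arm coefficient unchanged.

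**Conclusion.** Wrong as written; should-fix. In the additional GEE models of uptake, a variable recorded during the intervention is listed with covariates fixed before randomisation. With it included, the arm odds ratio does not estimate the effect of allocation. The article handles fear/anxiety and self-efficacy as intermediaries, with estimates both ways, but gives implementation no such treatment.

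The direction of the conclusion rests on the documents. Its size rests on assumed scores: a correlation with arm of about 0.7 to 0.97 and a variance inflation of about 2 to 14.5. The arm log odds ratio can lie anywhere from unbiased but imprecise, through about zero, to reversed in sign, depending on how much of the effect runs through implementation and whether better-run schools implement better. The primary Mantel-Haenszel test and the sample size are unaffected.

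**What to change.** In Primary outcome analysis, replace the sentence on implementation. State that the adjusted intervention effect comes from arm, the randomisation strata and pre-randomisation covariates only: previous uptake, school type, school size and SEIFA index.

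Report implementation in a separate analysis labelled exploratory. One option is a dose-response within intervention schools, read as observational because schools that implement well may differ in other ways. Another is an instrumental-variable analysis with randomised arm as the instrument, which requires that allocation affects uptake only through the implementation that is scored. In either case, say which logs make up the score.

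The cost is one or two sentences in the analysis section. No new data are needed, and neither the design nor the primary analysis changes.

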#### Secondary outcome analysis

Mean change in scores of knowledge, self-efficacy, fear/anxiety, and decision-making will be compared between groups using two-sample t-tests with appropriate adjustment for clustering. Baseline scores for knowledge will be taken from the control group. Proportion of consent form returns will be compared between groups prior to dose 1 using Chi-square test with appropriate adjustment for clustering. Time taken to vaccinate will be measured by nurses during each immunisation day in both intervention and control schools. It will be calculated as the mean time to vaccinate 50 students in intervention schools compared with control schools. Mean time to vaccinate will be compared between groups in both years of the study to determine effect of the intervention over time. We will investigate whether the intervention improves vaccination rates through its effect on fear reduction, and self-efficacy increase, by comparing estimates of the effect of the intervention both with and without adjustment for the possible intermediary variables of fear/anxiety, and self-efficacy. These logistic regression models will use GEE and robust standard errors to account for the clustering.

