## Trial methods

### Study design

Cluster randomised controlled trial occurring over two school years: 2013 and 2014.

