### Sample

The overall target sample is 40 schools with year-8 enrolments above 100 students, stratified by Government, Catholic, and Independent sectors and geographical location, with up to 20 schools recruited in each of two states, Western Australia (WA) and South Australia (SA).

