### Participants

Male and female students in their first year of high school (year 8 in participating states). Key school personnel in participating schools and immunisation nurses.

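### Comparing vaccination time between arms in each of the two years does not estimate whether the intervention's effect changed, and the article leaves open whether the same schools are seen in both years

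*Protocol article*

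**What the plan says.** The protocol article, under Secondary outcome analysis, fixes both a method and an inference for time taken to vaccinate: "Mean time to vaccinate will be compared between groups in both years of the study to determine effect of the intervention over time". It names no contrast between the two years.

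The rest of the article describes the time structure as follows:

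- Study design: "Cluster randomised controlled trial occurring over two school years: 2013 and 2014".
- Participants: "Male and female students in their first year of high school (year 8 in participating states"). Each calendar year therefore brings a new cohort of students.
- Sample: "The overall target sample is 40 schools with year-8 enrolments above 100 students".
- Abstract, Methods/Design: "aiming to recruit 40 schools with year-8 enrolments above 100 students (approximately 4400 students").
- Power calculation: "each school of the 36 schools would have 150 students giving a total final sample size of 5400 students".
- Primary outcome analysis: vaccination rates are compared "taking into account the stratification by year, state and school sector".
- Permuted block randomisation: the strata are state and sector, year is not among them, and schools are allocated in order of recruitment.
- Time taken to immunise: nurses log the time on each vaccination day, so this outcome is recorded by school and day, not by student.

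Nowhere does the article say whether a school takes part in one school year or in both.

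**The concern.** An effect over time is a difference between two effects: the arm difference in 2014 minus the arm difference in 2013. Comparing arms within each year yields the two components but neither the difference nor its uncertainty. Two arm differences can look unlike each other by chance while the underlying effect is constant.

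The meaning of the difference also depends on which schools supply each year. If the same schools are logged twice, the contrast describes the effect in a second year of use, and the two measurements from a school are correlated. If each school is in the trial for one year only, no school is observed in a second year of the intervention. The contrast then compares early-recruited with late-recruited schools.

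At stake is a secondary claim that the time saving from the intervention grew, faded or persisted. The primary outcome and the overall arm comparison of vaccination time are not affected.

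**Working it through.** **1. The plan's own sample size.** Inputs from Power calculation: "detection of a change in the percentage of students vaccinated from 70 to 80" per cent, ICC 0.05, power 80%, significance 0.05 (two-sided assumed, since the article does not say).

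- Two proportions, no clustering: 294 students per arm, or 313 with continuity correction.
- Design effect 1 + (m − 1) × 0.05. For m = 150 it is 8.45; for m = 110 it is 6.45.
- m = 150: 294 × 8.45 / 150 = 16.6, so 17 schools per arm (34). With continuity correction, 313 × 8.45 / 150 = 17.6, so 18 per arm (36).
- m = 110: 294 × 6.45 / 110 = 17.2, so 18 per arm (36).

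The stated 36 schools are reproduced. No stated figure is wrong.

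**2. How many cohorts per school do the totals hold?**

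- 5400 / 36 = 150 per school, and 4400 / 40 = 110 per school.
- Eligibility requires a year-8 enrolment above 100. Two cohorts per school would therefore exceed 2 × 100 × 36 = 7200 students in 36 schools, or 2 × 100 × 40 = 8000 in 40.
- At the article's own averages, two cohorts would be 2 × 150 × 36 = 10800 or 2 × 110 × 40 = 8800.

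Both stated totals fit one cohort per school. Listing year beside state and sector as a stratum fits this too.

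**3. Precision if each school is in one year.** Assumptions, none given in the article: 36 schools analysed, 18 per arm; an even split of 9 per arm per year; the same true effect in both years; school means with equal SD, used as the unit because no SD for vaccination time is stated; two-sided t-tests at 0.05.

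| Comparison | Standard error (SD units) | Detectable at 80% power |
|---|---|---|
| Arms, both years together | √(2/18) = 0.33 | 0.96 |
| Change in arm effect between years | √(4/9) = 0.67 | 1.93 |

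The ratio is 1.93 / 0.96 = 2.0. A constant effect of 0.96 SD, tested within one year with 9 schools per arm (standard error √(2/9) = 0.47), has about 48% power.

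**4. Precision if the same 36 schools are logged in both years.** For a correlation r between a school's two yearly means, the standard error of the change in arm effect is √(4(1 − r)/18). By the normal approximation (multiplier 2.80) the detectable change is 1.32 SD at r = 0, 0.93 at r = 0.5 and 0.42 at r = 0.9. The answer thus depends strongly on whether schools repeat and on using the pairing, and year-by-year comparisons do not use it.

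**The case against.** The strongest reply has three parts.

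First, one year per school is an inference. The student totals were set for vaccine uptake and do not limit a nurse log kept by school and day; the same schools could be timed in both years. Year as an analysis stratum fits separate schools per year but does not prove it. This stands. A reader might infer that the article commits each school to a single year, but it does not say so.

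Second, a reader might go further and conclude that the comparison cannot show any change over time. That is too strong. Even with different schools each year, the arm contrast within a year compares randomised schools, and the difference between the two contrasts can be estimated. It is imprecise and mixed with school differences and anything else that differed between the calendar years, but it is not empty.

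Third, the sentence does not prescribe two significance tests read against each other, and the exact model may be left to an analysis plan that is not shown. This stands in part. Under the assumptions in step 3 of the working, the chance that exactly one year is significant although nothing changed is 2 × 0.483 × 0.517 = 0.50. That figure describes a decision rule the article never adopts, so it is not counted as a consequence of the plan. What the reply does not remove is that the article itself states the method and the inference drawn from it, and the first does not deliver the second.

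**Conclusion.** The concern holds under either reading of the design. If schools repeat, the change in effect needs a contrast that accounts for repeated measurement of a school. If they do not, the years are represented by different schools not randomised to year, and the contrast shows at most whether the effect was consistent across recruitment years.

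The size is illustrative: about 48% power within each year, and a detectable change about twice the detectable main effect (1.93 against 0.96 SD of school means). It rests on the even split, the constant effect, and 80% power overall for an outcome on which the article gives no power statement. It concerns one sentence on one secondary outcome, and merits correction because a better method is available at little cost.

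**What to change.** - State, under Study design and Power calculation, whether a school contributes one year-8 cohort or two.
- Estimate one effect of allocation on vaccination time across both years, with year as a stratum and school as the cluster.
- Assess any difference between years only by the arm-by-year contrast, reported with its confidence interval.
- If the same schools are logged in both years, account for repeated measures by school.
- If each school takes part in one year, describe the contrast as consistency of effect across recruitment years, and delete the closing clause of the Secondary outcome analysis sentence that claims an effect over time.

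The cost is some wording and one model term. The downside is that the over-time claim becomes imprecise or is lost.

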### Data collection

Psychosocial outcomes will be measured using the HPV Adolescent Vaccination Intervention Questionnaire (HAVIQ). School personnel will administer the entire HAVIQ questionnaire (all four domains) after the students have participated in the education intervention session, but before they have had dose 1 of the HPV vaccine in intervention schools, and prior to dose 1 in control schools. Both groups of schools will complete the ‘Skills inventory’ and ‘Feelings towards vaccination’ components of the questionnaire before dose 2 of the HPV vaccine to measure the change in these domains after personal experience with vaccination. The ‘Knowledge’ component of the questionnaire will be given again prior to dose 3 of the HPV vaccine to measure knowledge retention over time. Self-reported vaccination status will be included in the questionnaire prior to dose 3.

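### Comparing logistic coefficients with and without fear/anxiety and self-efficacy understates mediation, because the coefficient shifts on adjustment even when nothing is mediated

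*Protocol article*

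**What the plan says.** Under Secondary outcome analysis, the article sets out to learn whether the intervention improves vaccination rates by lowering fear and raising self-efficacy. The stated method is "comparing estimates of the effect of the intervention both with and without adjustment for the possible intermediary variables of fear/anxiety, and self-efficacy". The model is fixed in the next sentence: "These logistic regression models will use GEE and robust standard errors to account for the clustering". No risk-difference standardisation and no other mediation estimator is named. The article does not use the term odds ratio, but a log odds ratio is what a logistic model returns by default.

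Three other places bear on this analysis:

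- **Planned uptake** (Power calculation): "A total of 36 schools allows for the detection of a change in the percentage of students vaccinated from 70 to 80" per cent.
- **Completeness of the mediators** (Power calculation): the detectable differences for the questionnaire scores allow for 40% "non-completion of these outcomes". Uptake itself comes from the State Health Departments, and student vaccination data are linked to the questionnaires by school-generated codes (Vaccination uptake).
- **Timing of the mediators** (Data collection): all four questionnaire domains are measured before dose 1. The fear and self-efficacy domains are repeated "before dose 2 of the HPV vaccine to measure the change in these domains after personal experience with vaccination".

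**The concern.** The planned comparison reads a drop in the intervention coefficient, once the mediators are added, as the part of the effect that runs through them. That reading needs a coefficient that stays put when a variable unrelated to the intervention is added. A logistic coefficient does not. It is conditional on whatever else is in the model, and it grows in absolute size when a predictor of the outcome is added. GEE with robust standard errors deals with correlation within schools. It averages over schools but still conditions on the covariates, so it does not remove this shift. The shift is negligible for rare outcomes, but uptake of 70% to 80% is not rare.

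Mediation pulls the adjusted coefficient towards zero, while non-collapsibility pushes it away. The planned comparison sees only the net result, so real mediation can appear as none or even as a negative share. Reducing anxiety and building confidence are stated purposes of the adolescent intervention. A falsely negative mechanism result could lead programs to drop components that work.

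**Working it through.** **1. The plan's own figure.** Inputs from Power calculation: 70% and 80% vaccinated; "at a significance level of 0.05 and with a power of 80" per cent (two-sided assumed); "assuming an intraclass correlation coefficient (ICC) of 0.05"; each school "would have 150 students giving a total final sample size of 5400 students".

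- Students per arm without clustering: [1.960·√(2·0.75·0.25) + 0.842·√(0.7·0.3 + 0.8·0.2)]² / 0.10² gives 294, or 313 with continuity correction.
- Design effect: 1 + 149 × 0.05 = 8.45.
- Schools per arm: 294 × 8.45 / 150 = 16.6, or 313 × 8.45 / 150 = 17.6, which rounds up to 18.
- Total: 2 × 18 = 36 schools, and 36 × 150 = 5400 students. The stated size is reproduced, so 70% against 80% is a fair basis for what follows.

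**2. Marginal effect.** OR = (0.80/0.20) / (0.70/0.30) = 4 / 2.333 = 1.714; log OR t = 0.539.

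**3. Adjusted effect with no mediation.** Let fear/anxiety and self-efficacy together add a normal term with SD s to the logit of vaccination, with the same distribution in both arms. Find intercepts a₀ and a₁ so that the average of expit(a + s·Z) over standard normal Z is 0.70 and 0.80 (80-point Gauss-Hermite integration). The adjusted log OR is c = a₁ − a₀. The value of s is an assumption. For orientation, two independent, equally strong variables each have an OR per SD of exp(s/√2).

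| s | OR per SD, each variable | a₀ | a₁ | c | Adjusted OR | c/t − 1 |
|---|---|---|---|---|---|---|
| 0.3 | 1.24 | 0.865 | 1.413 | 0.548 | 1.73 | +2% |
| 0.5 | 1.42 | 0.895 | 1.459 | 0.564 | 1.76 | +5% |
| 1.0 | 2.03 | 1.018 | 1.650 | 0.631 | 1.88 | +17% |
| 1.5 | 2.89 | 1.188 | 1.916 | 0.729 | 2.07 | +35% |

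In every row the risk difference averaged over Z is still 0.80 − 0.70 = 0.10. The shift belongs to the logit scale alone.

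**4. What the comparison would report.** If a share f of the conditional effect c is truly mediated, the adjusted log OR is (1 − f)·c, and the apparent share is 1 − (1 − f)·c/t. At s = 1:

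- f = 0: 1 − 0.631/0.539 = −17%.
- f = 15%: 0.85 × 0.631 = 0.537 against 0.539, so about 0%.
- f = 30%: 0.70 × 0.631 = 0.442; 1 − 0.442/0.539 = 18%.

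**5. If the two models used different students.** Under the 40% allowance, the mediators would exist for 0.60 × 5400 = 3240 students. A GEE simulation with no mediation (36 schools of 150, 50 replicates) compared an unadjusted model on all students with an adjusted model on completers.

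- **Completion at random:** the change of sample alone did nothing material (unadjusted OR 1.65 against 1.66 at an OR of 1.5 per SD; 1.73 against 1.73 at 2 per SD).
- **Completion dependent on vaccination and arm** (assumed 65% of vaccinated students; 50% and 40% of unvaccinated students in intervention and control): the OR went from 1.73 unadjusted to 1.43 adjusted at 1.5 per SD, and from 1.75 to 1.50 at 2 per SD. The apparent shares are 1 − ln 1.43/ln 1.73 = 35% and 1 − ln 1.50/ln 1.75 = 27%, when the truth is zero.

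This error can therefore run opposite to the one in step 4.

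**The case against.** The strongest objection is about size. The distortion depends on how strongly student fear and self-efficacy predict vaccination, and the article gives no figure for that. It does say that parental consent is required, that no separate adolescent assent is needed, and that adolescents seldom take part in the decision. A weak link is therefore plausible, and at s = 0.3 to 0.5 the shift is only 2% to 5%. This stands, and it is why the result is given as a range. It does not rescue the method, because mediation through these variables requires them to predict vaccination, and the distortion grows as they do.

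A reader might also infer more than the article supports:

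- **That the two models will use different students.** The article does not say so. Vaccination data are linked to questionnaires, so a common sample is available, and the 40% is a sample-size allowance, not a forecast. The choice of sample is open, not wrongly made.
- **That post-dose-1 scores will be used as mediators of uptake that includes dose 1.** No section says this. Both domains are measured before dose 1, and the later round has its own stated purpose.
- **That the whole analysis is biased towards finding no mediation.** This holds for the scale problem only. Selective completion could push the other way.
- **That this is the only quantitative evidence on mechanism.** The article also compares the scores between arms, includes level of implementation in the models and plans qualitative work. The score comparisons show whether the intervention moves fear and self-efficacy, but not whether that moves uptake.

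**Conclusion.** The point holds for the effect scale. The article fixes a with/without comparison of logistic GEE effects for an outcome planned at 70% to 80%, and that comparison understates the mediated share. With no mediation, an OR of 1.71 becomes 1.73 to 2.07 over the assumed range (log OR +2% to +35%). At s = 1 the method misses a 15% share entirely and reports a 30% share as 18%. These figures assume normally distributed mediators with equal spread in both arms. The strength of association is assumed, not documented.

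Which students enter each model and which time point supplies the mediators are unspecified. They are worth settling as part of the repair but are not errors in the plan. The primary comparison of vaccination rates is unaffected. The change is worth making because the mechanism result is otherwise hard to interpret and the better method is cheap.

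**What to change.** Replace the comparison of logistic coefficients with one on a collapsible scale. The logistic models can stay, with predictions averaged to give standardised risk differences with and without the mediators, or a counterfactual mediation estimator can be used for direct and indirect effects. Take confidence intervals from a bootstrap that resamples whole schools.

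State alongside it:

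- Both estimates use the same students, namely those with linked questionnaire and vaccination data.
- When the outcome includes dose 1, the mediators are the pre-dose-1 scores.
- Restricting to completers makes the samples equal but does not remove selection bias if completion depends on vaccination and arm. Report completion by arm and vaccination status.
- Unmeasured mediator-outcome confounding, for example by parental attitude, remains possible and should be acknowledged.

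The cost is a little more analysis work. It needs no new data, and school numbers and the primary analysis do not change.
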